**Parent consent for adolescent participation and own participation:**

Parents will receive a letter containing information about the study from their child’s school (for ISY) or from a youth-serving CBO (for OOSY). Next, for ISY participants, interviewers from KSPH will host a parent information session at the school that will describe the study goals and procedures and the risks and benefits of participating. In addition, they will be explicitly informed of their child’s confidentiality and the procedures in place in the event of disclosure of abuse. Specifically, parents will be told that their child’s ongoing exposure to physical and/or sexual abuse will require further investigation and potential disclosure to legal and/or child protection services. They will also be informed that participation is voluntary, and their child can end participation in the study at any time with no penalty.

In order for a child to participate, his or her parent must agree to participate in a brief baseline survey module for the collection of sociodemographic data about themselves and their family. The purpose of this is to increase accuracy in reporting and decrease burden on the adolescent participant. The researcher obtaining consent will describe this portion of the study at the time of obtaining consent for adolescent participation and will describe the risks and benefits of participation.

If parents agree for their child to participate and to participate themselves, the researcher will obtain written informed consent from the parent; or, in the event that they are unable to sign, they may make their mark. The parent will be provided a copy of the informed consent form to keep with contact information of the study staff including the field coordinator, the site-PI, and the JHBSPH study coordinator ([name]) for reference. The researcher or community liaison will serve as a witness to the consent process and will counter-sign the forms to indicate that they properly obtained consent from the parent.

**Adolescent assent:** After obtaining parental consent, KSPH researchers will visit participating schools (for ISY) or community centers (OOSY) to collectively explain the purpose of the study to adolescents whose parent provided consent for their participation and will describe the risks and benefits of being in the study, what type of information will be collected, and which types will be confidential and which, if reported, will not (e.g., participant report of physical/sexual abuse). They will also be informed that they are free to choose if they want to participate and that they can discontinue participation at any time with no penalty. Adolescents will be provided an assent form that contains the same information provided to parent including possible risks and benefits of the study, a description of the kind of information asked, and which kinds of information are confidential and which are not. Specifically, adolescent assent will occur in a private conversation with an interviewer who will tell the adolescent will be told, “If you indicate that you have been hurt or harmed in any way, we will need to stop the interview and I will need to let my supervisor know so that we can be sure you are not in ongoing danger.” If the adolescent agrees to participate, the researcher will obtain written informed consent; or, in the event that they are unable to sign, they may make their mark. The adolescent will be provided a copy of the assent form to keep with contact information of the study staff including the field coordinator, the site-PI, and the JHBSPH study coordinator ([name]) for reference. The researcher or community liaison will serve as a witness to the assent process and will counter-sign the forms to indicate that they properly obtained assent from the adolescent.

2. Identify the countries where the research will take place, and the languages that will be used for the consent process.

| **Country** | **Consent Document(s)**  **(adult consent, parental permission, youth assent, etc.)** | **Languages** |
| --- | --- | --- |
| DRC | Adolescent assent | French & Lingala |
| DRC | Parental consent for child participation & own participation | French & Lingala |

C. Study Implementation:

Answer the following:

1. Describe the procedures that participants will undergo. If complex, insert a table below to help the reviewer navigate.

Participants in the intervention arm will take part in an intervention program (GUG), which was found to produce positive outcomes in Uganda and Nepal and has been adapted for use in Kinshasa by Save the Children. Save the Children will hire and train staff from youth-centered CBOs to implement out-of-school components and will train teachers on how to use the in-school components. Parents of youth in the intervention arm will be invited to take part in one component. Participants will be engaged in the intervention will be in place for one school year.

Participants in both the intervention and control arms will take part in a baseline survey and will be surveyed again every 6 months over a period of 4 years.

Parents in both study arms will take part in a baseline questionnaire.

2. Describe the number and type of study visits and/or contacts between the study team and the participant, how long they will last, and where/how they will take place.

Follow-up surveys will be given every 6 months over a period of 4 years. While the baseline survey may take up to 1.5 hours to complete, follow-up surveys will last not more than 45 minutes. In-school adolescents will be surveyed at school or a nearby community center, and out-of-school adolescents will be surveyed at a local community center. The survey will primarily be interviewer-facilitated, but CASI/ACASI will be used for certain sections for increased privacy, as noted above.

All parents of participating youth will complete a short questionnaire with an interviewer at the time of consent; these interviews will be conducted in either French or Lingala as the participant prefers and last not more than 15 minutes.

Our partners at KSPH work closely with community liaisons who know participants, their families, and their locations. Parental contact information will be securely stored and used to contact parents of participants who have moved. If necessary and possible, the survey may be conducted by phone. Otherwise, the participant will be among those lost-to-follow up.

3. Describe the expected duration of the study from the perspective of the individual participant and duration overall.

Five years overall, with the participant involved for 4 years of data collection.

4. Provide a brief data analysis plan and a description of variables to be derived.

Initially at baseline descriptive analyses will be done to test for comparability of intervention and comparison groups. Subsequently bivariate statistics (Chi-Square and Student’s t-test) will be run exploring the relationships between independent variables and key outcomes. Finally multivariate analyses will be performed to evaluate associations between gender norms, empowerment and the primary outcomes of interest sexual behaviors and outcomes, gender based violence and mental health. Over time, tests of differences will be run exploring change in gender equitable attitudes, gender norms and how these changes predict changes in prevalence of gender based violence and contraceptive utilization between intervention and control groups.

5. Describe whether you are collecting or storing personal identifiers, and if yes, why you need them, and when and how you plan to dispose of them. Signatures on consent forms are considered to be identifiers.

Participants will be assigned a unique identifier, which will be recorded with their responses during electronic data collection. A separate document containing participant’s photograph, identification number, name, age, and location will be kept in a locked file cabinet at KSPH for data collectors to contact participants for follow-up. These will be retained with consent and assent forms in a dedicated and locked cabinet that will only accessed by the site PI and the study coordinator. All electronic data will be encrypted. All documents with contact information will be destroyed immediately following the last wave of data collection and only coded data without any identifiers will be retained.

6. Answer the following **if they are relevant to your study design**

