This longitudinal phase builds on the first by exploring how gender norms relate to health across the adolescent years, beginning with early adolescence. The GEAS in Kinshasa has two sets of objectives: 1) To explore how perceptions of gender norms evolve across adolescence, the factors influencing these changes, and how perceptions of gender norms predict a spectrum of adolescent outcomes, and 2) Assess the impact of a gender norms transformative intervention developed and implemented by Save the Children. The intervention, Growing Up GREAT (GUG), and evaluation components are part of a larger project, *Passages*, which is led by the Institute for Reproductive Health (IRH) at Georgetown University. Our research partner is the Kinshasa School of Public Health (KSPH), which will implement the GEAS study. The Kinshasa component of the project has both USAID and Gates Foundation support.

In both an intervention and control group 1,400 young people ages 10-14 will be followed over a period of 4 years, with one additional year of data analysis. To gauge effectiveness of the intervention, we will assess the following measurable primary and secondary study outcomes:

Primary outcomes:

- Doubling of contraception use among sexually active youth
- 10% decrease in reports of exposure to gender-based violence (GBV) compared with the previous 6 months

Secondary outcome:

- 20% shift toward more gender-equitable attitudes and beliefs

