**III. Study Design**

**Overview of study design and methods.** The GEAS in Kinshasa will involve a quasi-experimental longitudinal (pretest-midline-posttest) design to compare changes in perceptions of gender norms and subsequent effects on adolescent health outcomes between a group of early adolescents receiving Save the Children’s GUG intervention and a non-intervention control group. The control group is an essential feature of the study and will allow the exploration of developmental changes in adolescent health in the absence of an intervention during this critical period of human development.

The selection of intervention and control groups, which will include a sample of both in-school youth (ISY) and out-of-school youth (OOSY), will be based on geography, school selection (the ISY samples), and self-selection of adolescents participating in the intervention activities, described in detail in Section IV, “Participants” below. All participants will complete a baseline survey (before the intervention begins) and will be surveyed every 6 months over a period of 5 years. The survey will be divided into 2 segments, each collected 6 months apart in order to collect a complete wave of data every year. Additionally, this approach will minimize respondent burden and minimize loss to follow-up due to frequency of contact. Starting with the second wave, the survey instrument will be modified to include questions appropriate for older adolescents, and at that time a supplemental IRB application/amendment will be submitted. Following the same procedure as in the Phase 1 pilot, data collection will be conducted by trained interviewers using mobile tablets with the capacity for face-to-face interview also known as CAPI (computer-assisted personal interview), computer-assisted self-interview (CASI), and/or ACASI (audio computer-assisted self-interview) survey administration. When CAPI is the primary administration method, CASI/ACASI will be used for potentially uncomfortable questions, such as those about adverse childhood experiences and sexual and reproductive health, in order to increase privacy and improve data quality. We will continue to use the secure survey design and data collection software (SurveyCTO) used during the Phase 1 pilot test, which greatly improves data security over other methods.

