Next, the school-parent committee (PTSA) will send a letter to parents of selected students informing that their child has been selected for participation in the study and indicating that interviewers from KSPH will be hosting an information session with a given date and time at the school. The parent information session will describe the study goals and procedures, and the risks and benefits of participating. In addition, they will be explicitly informed of their child’s confidentiality and the procedures in place in the event of disclosure of abuse. Parents will be asked at the end of the session if they consent for their child to participate and if they themselves consent to participate in the baseline questionnaire. If parents give consent to both, they will be asked to complete the short (15 minute) questionnaire, either by themselves (CASI) if they can read and navigate a tablet on their own, or with the help of an interviewer (CAPI).

After parents have provided consent for their children’s participation, adolescents will be informed and reminded by their teachers regarding the time and place of data collection and whether it will take place in the school facilities or in a communal area (church or community building) near the school, depending on the availability school facilities. All adolescents from the same school will be convened at the same time. Before data collection, the adolescents will be collectively informed about the study goals, procedures, and the consent procedure including the protocol for child abuse disclosure. At the end of the information session, children will have an individual conversation with his/her interviewer in order to assent to participate. After assent has been given, data collection will proceed.

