Intervention activities will be available and open to youth enrolled in the study and also whom are not. That is, participants enrolled in the intervention group will be encouraged to participate, but they will do so alongside peers who may not be enrolled for any reason.

Regarding participation in the survey itself, participants will be given as much privacy as possible, and data collection will occur in unobtrusive times/settings (i.e. participants will not miss class or be singled out), but it cannot be guaranteed that their involvement in the study will be private. Adolescent participants and their parents will be made aware of this fact at the time of consent/assent, as well as of the fact that they are free to leave the study at any time without penalty.

1. Consent Process:

After parents have been notified of the study as described in Section A above, KSPH researchers will be responsible for obtaining parental consent and youth assent. These researchers are trained in research ethics and best practices, and will have been CITI certified in advance of recruitment, consent, and baseline data collection.

With the assistance of school directors and PTSAs, KSPH researchers will organize informational meetings for parents of eligible ISY at which consent for participation will be sought. With the assistance of youth-serving CBOs familiar with community members and other community representatives, KSPH data collectors will visit the homes of OOSY to inform parents of eligible adolescents about the study goals, procedures, risks and benefits and the opportunity to participate. Both parents and adolescents will be aware before the time of consent of whether the adolescent participant would be in the intervention or control arm of the study.

The researcher will obtain written informed consent from the parent for the adolescent’s participation and their own participation; or, in the event that they are unable to sign, they may make their mark. The parent will be provided a copy of the informed consent form to keep with contact information of the study staff for reference. The researcher or community liaison will serve as a witness to the consent process and will counter-sign the forms to indicate that they properly obtained consent from the parent. The same process will be conducted to obtain assent from the adolescent prior to baseline data collection.

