As noted above, some information collected as part of the GEAS is personal, and participants will be informed that this information is confidential and that they have the right to refuse answering questions or sections of the survey without prejudice. Participants will be asked questions about a range of topics including family, school, sexual attitudes and behaviors, mental health, and adverse childhood experiences any of which may make them uncomfortable. It should be noted that the modules on adverse childhood experiences and on sexual and reproductive health will be completed using CASI/ACASI rather than by interviewer so that the data are directly entered by the adolescent into the tablet. As noted previously, data collectors will undergo a 5-day training prior to data collection to learn among other things how to recognize if participants are feeling significant distress. Data collectors will be informed that if an adolescent participant experiences signs of distress, they will immediately remind the participant that they do not need to answer any questions that make them feel uncomfortable. If the respondent decides to stop, the data collector will notify the field coordinator who will notify the respondent’s parent/guardian of the situation. If he/she asks to continue the data collector will do so; however, if discomfort is expressed a second time the data collector will cease data collection and will notify the field coordinator immediately. Additionally, the young person and parent/guardian will be provided resources for help if needed.

In all cases, data collectors will be required to record if a participant experiences distress and inform the field coordinator who will advise the site PI. Where there is suspicion or evidence of physical or sexual abuse the data collector will be instructed to stop the interview, inform the subject of his/her concern and notify the field coordinator and site PI. If the site PI determines that the situation warrants follow up he will contact the designated child protection agency and concurrently notify the Hopkins PI who in turn will notify the JHBSPH IRB detailing the steps being taken to protect the child. Where the abuse may involve a parent or family member the report will go directly to the field coordinator/PI however if it does not, the parent will also be informed. Additionally, a detailed child protection protocol specific to Kinshasa is in place.

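### By default the gender-norm scales are asked by an interviewer, in adolescents who know their arm and of whom only one arm was taught the construct; differential reporting could mimic the detectable difference in Table 3

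*Protocol*

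**What the plan says.** **Survey mode.** Section V.C (Study Implementation), item 2, gives the default: "The survey will primarily be interviewer-facilitated, but CASI/ACASI will be used for certain sections for increased privacy". Section III gives the criterion for leaving that default: "CASI/ACASI will be used for potentially uncomfortable questions, such as those about adverse childhood experiences and sexual and reproductive health". Section VII is firmer about which modules leave it: "the modules on adverse childhood experiences and on sexual and reproductive health will be completed using CASI/ACASI rather than by interviewer". The gender-norm scales are named in neither place.

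**Knowledge of arm.** Section V, Consent Process: "Both parents and adolescents will be aware before the time of consent of whether the adolescent participant would be in the intervention or control arm". No masking of interviewers is described.

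**What one arm is taught.** The second study objective in Section I is to "Assess the impact of a gender norms transformative intervention developed and implemented by Save the Children". Section III compares this with a control group that gets no intervention.

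**Role of the scales.** Section I makes a 20% shift in gender-equitable attitudes the secondary outcome. The analysis plan in Section V.C, item 4, uses change in attitudes and norms to predict change in gender-based violence (GBV) and contraceptive use. Table 3 gives detectable differences of 0.14 (SD 0.59) and 0.17 (SD 0.69) on two scales.

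**The concern.** Three features coincide for this outcome: the answer is self-reported, the default mode puts an interviewer in front of the respondent, and one arm has been taught which answers are approved. Adolescents in that arm may report more equitable attitudes without holding them, and controls have no comparable cue. The difference would arise only after the curriculum, so adjustment for baseline scores would not remove it. Nor could a later analysis plan, because mode is fixed when the data are collected. The secondary outcome would be affected directly. The analysis that links attitude change to GBV and contraception would be affected through its predictor.

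**Working it through.** **Inputs** (Sample size and justification, Table 3): 40 clusters of 20 per arm after attrition, so 800 per arm; ICC 0.15; power 80%; scale 1 mean 3.99, SD 0.59; scale 2 mean 3.55, SD 0.69; alpha 0.05. Alpha is stated for the two primary outcomes and assumed here for attitudes; its sidedness is not stated.

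**Step 1: reproduce the plan's figure.**
- Design effect = 1 + (20 − 1) × 0.15 = 3.85; effective n = 800/3.85 = 207.8 per arm.
- SE of the difference = SD × √(2/207.8): 0.058 (scale 1) and 0.068 (scale 2).
- Detectable difference = (z for alpha + z for power) × SE. One-sided alpha 0.05 gives 0.144 and 0.168, which matches the stated 0.14 and 0.17. Two-sided alpha gives 0.162 and 0.190.

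The plan's figures are therefore recovered with a one-sided test. The steps below use the two-sided 0.05 threshold, which is the stricter one for a false positive.

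**Step 2: put the detectable differences in SD units.** 0.14/0.59 = 0.24 SD; 0.17/0.69 = 0.25 SD.

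**Step 3: find the smallest observed difference that is significant.** 1.96 × SE = 0.11 and 0.13 points, about 0.19 SD on either scale.

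**Step 4: assume no true effect and a reporting shift b (in SD units) in the intervention arm only.** SE in SD units is √(2/207.8) = 0.098. The probability of a significant favourable result is 1 − Φ(1.96 − b/0.098). The documents give no size for b, so a range is shown.

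| Assumed shift b | Probability of a significant favourable result |
|---|---|
| none | 2.5% |
| 0.10 SD | 17% |
| 0.15 SD | 33% |
| 0.20 SD | 53% |
| 0.25 SD | 72% |
| 0.30 SD | 86% |

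**Step 5: compare with the larger effects in the text**, read as a percentage of the control mean.
- 20% shift (Section I): 0.20 × 3.99 = 0.80 points, or 1.35 SD; 0.20 × 3.55 = 0.71 points, or 1.03 SD.
- 10% shift (sample size text): 0.40 points, or 0.68 SD; 0.36 points, or 0.51 SD.

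A bias as large as Table 3's detectable difference would be 0.14/0.80 = 18% and 0.17/0.71 = 24% of the 20% target.

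**The case against.** **Mode is inferred.** A reader might conclude that the protocol prescribes face-to-face questions on gender attitudes. It does not say so. Section III allows interviewer and self-completed administration and its list of sensitive topics is open-ended. The survey instrument, Appendix 1, might settle the mode but is not shown. This stands as a limit on the claim. Still, the default is clear, and attitude items do not obviously meet a criterion framed around discomfort and privacy.

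**GBV.** A reader might infer that this primary outcome is asked aloud. The documents do not support that: the Consent Process section treats GBV and abuse as sensitive data, so the Section III criterion plausibly covers these items already. Contraception plausibly sits in the self-completed sexual/reproductive health module. The point therefore rests on the secondary outcome.

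**Teachers and the implementer.** A reader might infer that programme staff influence the sessions. Save the Children "will train teachers on how to use the in-school components", and "adolescents will be informed and reminded by their teachers regarding the time and place of data collection". But the reminder concerns logistics only, it applies equally in control schools, and no text places teachers or Save the Children staff in survey sessions. Data collection belongs to KSPH, which is not the implementer.

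**Size.** A quarter of an SD is far below the 20% target, and equating bias with the detectable difference says nothing about how large the bias is. Both are correct. Step 4 shows only that a modest shift would be enough for a false positive.

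**Mitigation.** The programme lasts one school year, while Section V.C plans surveys over four years, so many measurements fall well after teaching ends. That may weaken the bias, but it leaves the interviewer in place for these items.

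**Conclusion.** The point holds for the gender-norm scales. Under the protocol's default mode they would be interviewer-administered, arm is known, and only one arm is taught the construct being measured. An arm-specific reporting shift of 0.24 to 0.25 SD would equal Table 3's detectable differences, and about 0.19 SD already reaches two-sided significance. The probabilities rest on the plan's ICC and sample size, a normal approximation, and assumed bias sizes. The documents do not show that such bias will occur. Nor do they support reading the whole 20% shift as explicable by it, since that would need a reporting shift of 1.03 to 1.35 SD. This is a weakness worth correcting before baseline; it does not invalidate the study.

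**What to change.** **In Sections III, V.C (item 2) and VII:**
- Add the gender-norm scales to the CASI/ACASI block, in both arms and from baseline onward, so that mode is constant across arms and over time.
- Confirm that the GBV items are in the same block.
- State that each KSPH interviewer works in both arms.
- Flag any survey done by phone, which Section V.C permits, because its mode will differ.

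**Cost:** audio for the added items in French and Lingala where ACASI is used, a few more minutes of self-completion, and help with the tablet for the youngest. If the pilot scales were interviewer-administered, some comparability with the pilot means and SDs behind Table 3 is lost. A change after baseline would confound mode with time, so it needs to be made before then.

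**Limit:** self-completion removes the interviewer's presence but not knowledge of the taught answers. The protocol should say that attitude results will be interpreted with that in mind.
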